# Implementing training and support, financial reimbursement, and referral to an internet-based brief advice program to improve the early identification of hazardous and harmful alcohol consumption in primary care (ODHIN): study protocol for a cluster randomized factorial trial

**DOI:** 10.1186/1748-5908-8-11

**Published:** 2013-01-24

**Keywords:** Alcohol, Screening, Brief interventions, Primary healthcare, Training and support, Financial reimbursement, Internet, Implementation

## Abstract

**Background:**

The European level of alcohol consumption, and the subsequent burden of disease, is high compared to the rest of the world. While screening and brief interventions in primary healthcare are cost-effective, in most countries they have hardly been implemented in routine primary healthcare. In this study, we aim to examine the effectiveness and efficiency of three implementation interventions that have been chosen to address key barriers for improvement: training and support to address lack of knowledge and motivation in healthcare providers; financial reimbursement to compensate the time investment; and internet-based counselling to reduce workload for primary care providers.

**Methods/design:**

In a cluster randomized factorial trial, data from Catalan, English, Netherlands, Polish, and Swedish primary healthcare units will be collected on screening and brief advice rates for hazardous and harmful alcohol consumption. The three implementation strategies will be provided separately and in combination in a total of seven intervention groups and compared with a treatment as usual control group. Screening and brief intervention activities will be measured at baseline, during 12 weeks and after six months. Process measures include health professionals’ role security and therapeutic commitment of the participating providers (SAAPPQ questionnaire). A total of 120 primary healthcare units will be included, equally distributed over the five countries. Both intention to treat and per protocol analyses are planned to determine intervention effectiveness, using random coefficient regression modelling.

**Discussion:**

Effective interventions to implement screening and brief interventions for hazardous alcohol use are urgently required. This international multi-centre trial will provide evidence to guide decision makers.

**Trial registration:**

ClinicalTrials.gov. Trial identifier: NCT01501552

## Background

The European Union (EU) has the highest alcohol consumption of the world: in 2009, the average adult (aged 15+ years) alcohol consumption in the EU was 12.5 litres of pure alcohol [1]. A review showed that consumption above 20 to 30 grams of alcohol a day (two to three glasses of wine) increases an individual’s risks of mortality and morbidity [2,3]. However, people often overestimate the positive health effects of alcohol; in fact, only small amounts of alcohol have positive effects on health [2,3].

Alcohol consumption is the third world leading cause of diseases and premature death [1]. The costs related to alcohol are €125bn a year for health, welfare, employment, and criminal justice sectors as a consequence of alcohol-attributable disease, injury, and violence [4]. Therefore, individuals and society would benefit from effective preventive measures with respect to morbidity and mortality and social costs.

There is considerable evidence showing that early identification of hazardous and harmful alcohol consumption result in reduced alcohol consumption and improved health outcomes. Primary healthcare (PHC) is the primary point of contact for many people seeking healthcare. In this setting, screening [5] and brief intervention programs have proven to be effective in reducing alcohol consumption [6-10], with a mean reduction of 38 grams of alcohol per week (three to four glasses of wine) [10]. Although the evidence is still inconsistent about positive effects of nurse-led interventions [11,12], generally screening and brief interventions are provided by healthcare workers such as GPs, nurses, or psychologists [10]. The number needed to treat (NNT) in offering screening and brief interventions is eight (for every eight people treated one will change their behaviour) [13], which is relatively low compared to smoking cessation, which has a NNT of around 35 or higher [14]. Despite the evidence for efficacy and cost-efficacy of screening and brief interventions in PHC, these interventions are rarely implemented in routine practice [15]. Commonly, less than 10% of the population at risk are identified, and less than 5% of those who could benefit are offered screening and brief interventions in PHC settings [15].

Some of the reasons for this gap are identified and can be categorised in three main domains. First, evidence suggests there is substantial lack of knowledge among general practitioners (GPs) [5,16]. A survey across 13 countries found that one-third of all GPs reported never receiving alcohol-related education, 23% reported less than four hours, and 37% reported more than seven hours of alcohol-related education ever [17]. A recent update from England has shown that 52% of the United Kingdom’s surveyed GPs indicated that they had received less than four hours of post-graduate training, continuing medical education, or clinical supervision on alcohol and alcohol related problems [18]. Furthermore a lack of role security and therapeutic commitment has been identified [19].

Secondly, lack of adequate resources and support are identified as important barriers [16,20]. Financial reimbursement could be important measures to overcome this barrier, but as far as we know, there have been no randomised controlled trials conducted investigating the impact of reimbursement for alcohol screening and brief interventions in the PHC setting.

The third important barrier relates to time constrains in terms of perceived workload and work pressure for screening and brief intervention activities [5]. In PHC, trained nurses are increasingly involved in preventive care activities and in the management of chronic ill patients due to the increased workload of GPs. It has shown that they provide safe and effective care [21]. This study focuses on all healthcare professionals working at primary healthcare units (PHCUs).

Although previous implementation studies [22,23] have tried to increase screening and brief interventions in primary healthcare, the gap between scientific knowledge and everyday clinical practice remains [24]. With regard to the first category of barriers of knowledge and attitude, earlier studies found that training and support could make GPs even less secure in their work with drinkers, when the training and support does not address prior GP’s attitude in the training and support [15,19]. In the ODHIN study, we will tailor our implementation strategy to the primary healthcare worker’s prior attitude. With regard to the second category, lack of resources, there are mixed results of evidence of finance systems to change provider behaviour [25,26]. There is limited evidence that finance systems can change provider behaviour of screening and brief interventions of alcohol [15]. Still, financial incentives for smoking cessation interventions have shown a significant positive outcome on increases in referral to tobacco cessation services [27], and suggest financial support for alcohol interventions might be effective. In the third category, workload and work pressure, we suggest e-health interventions might be of benefit. E-self help interventions without therapist support are available both in brief and more extended formats and have shown to be effective in reduction of alcohol consumption [28]. Additionally, internet interventions with therapist support focused on depression and anxiety were found to have larger effect sizes compared to internet interventions without therapist support [29], but has not yet been tested for alcohol internet interventions. These e-health interventions might be helpful to reduce workload of healthcare professionals after identification of patients at risk as well as availability for patients 24 h a day. Therefore, it is of interest to test if primary healthcare workers’ referral to internet-based brief interventions, hereafter termed e-BI, could be time-saving for healthcare professionals and consequently might raise primary care worker’s intervention activity.

It is of significant public health interest to explore, and optimize, effective implementation strategies to improve PHC activities in screening and brief interventions for hazardous and harmful alcohol consumption. In the current study, we evaluate the effect of three strategies, each aimed to tackle one of the above reported barriers, singly or in combination, in order to overcome the gap between knowledge and daily practice.

### Aim and objectives

Our aim is to study the effectiveness of training and support (T&S), financial reimbursement, and internet based brief interventions (e-BI), targeted singly or in combination to primary healthcare units, on screening and brief intervention activities, compared to treatment as usual. The following hypotheses will be tested in the study:

1. Provision of training and support to primary healthcare providers will increase use of preventive screening and brief interventions compared to a care as usual control group.

2. Financial reimbursement to primary healthcare providers as a pay-for-performance of brief alcohol interventions will increase screening and brief intervention rates compared to care as usual.

3. Providing resources, *i.e.*, offering referral possibility to an internet-based method of delivering brief intervention, will increase screening and brief intervention rates compared to care as usual.

4. The combination of training and support, financial reimbursement, and e-BI will be more effective in increasing screening and brief intervention rates compared to single-focused implementation strategies.

## Methods

### Design

Our study is designed as a cluster randomized factorial trial. Data from PHCUs in Catalonia, England, the Netherlands, Poland, and Sweden will be combined to examine the effect of three different implementation strategies singly or in combination on screening and brief advice rates for hazardous and harmful alcohol consumption compared with care as usual (controls). In all countries, the complete trial will be conducted between August 2012 and December 2013.

### Participants

PHCUs with approximately 5,000 to 20,000 registered patients will be the unit of randomization and implementation. In Poland, because practitioners normally operate as single-handed entities working with other practitioners in one building, three practitioners and their staff working in one building will be the unit of randomization. PHCUs who agree to participate in the study are volunteers that will be drawn from administrative or academic registries of PHCU at national or regional levels. PHCUs that have current ongoing alcohol-related projects that have a focus on screening and brief interventions, involve GPs and/or nurses, and include one of the ODHIN implementation strategies, will be excluded.

Besides fully-trained GPs, nurses or practice assistants with a permanent appointment working in the PHCU and involved in medical and/or preventive care are also eligible, because they also have skills to assist in screening and brief interventions [12,30,31]. At the start of the study, all eligible providers within the PHCU will be identified by the research team. Participating providers are those eligible providers who agree to participate in the trial. Before baseline measurement, the participating providers have to sign up for the study, allowing PHCU with a high number of staff to include only a selection of staff. Staff not able to attend this meeting but willing to participate will be informed by the contact person in the PHCU. These providers will also sign an informed consent for their participation. In the Netherlands, England, Poland and Sweden, PHCU will receive a trial fee. The trial flow chart is shown in Figure 1.

**Figure 1 F1:**
[figure not shown]
Trial flow chart is required.

### Implementation strategies

The implementation period will last twelve weeks, with the start date for each country between November 2012 and March 2013. The start date of the implementation period for each PHCU will be staggered. Implementation strategies are outlined in detail in Table 1. All groups will receive the same input as controls but with additional components added. These strategies are about to be tested singly or in combination:

1. Control group, treatment as usual

2. T&S

3. Financial reimbursement

4. e-BI

5. T&S and financial reimbursement

6. T&S and e-BI

7. Financial reimbursement and e-BI

8. T&S, financial reimbursement, and e-BI

**Table 1 T1:** Outline of intervention groups with three different implementation strategies

1.	Control Group—treatment as usual: The control group will receive a package, either hand-delivered or by post, containing a summary card of the national guideline recommendation for screening and brief advice for hazardous and harmful alcohol consumption, without demonstration. In Poland, where no national guidelines exist, the summary card will be adapted from the PHEPA guidelines for the purposes of this trial [33]. No further instructions will be given.
2.	Training and support: Countries differ largely with regard to usual T&S and other educational training of primary care staff. To maximise comparability, a set of minimal and maximal criteria have been established, in which each country specific T&S package should fit.
	In addition to receiving the same package as the control group, the T&S group will be offered two initial 1 to 2 hours face-to-face educational trainings, and one (10 to 30 min) telephone support call to the lead PHCU contact person during the twelve week implementation period. If necessary, one additional face-to-face training of 1 to 2 h duration will be offered. The time intervals between the initial training, the telephone call, and the additional optional training will be, on average, two weeks. The training addresses knowledge, skills, attitudes, and perceived barriers and facilitators in implementing screening and brief advice, combining theory and practical exercises. The location of the educational training will vary from country to country and include in-house meetings at the PHCU or within clusters of PHCUs. The trainers will include peer trainers, members of the research team, accredited teachers, or addiction consultants. Each country will use an adapted existing country-based T&S package. In the case of Poland, the T&S package will be based on the PHEPA training program.
3.	Financial reimbursement: In addition to receiving the same package as the control group, financial reimbursement groups will be paid for their registered screening and brief intervention activities. Payment depends on normal country specific fees and rates for financial reimbursement for clinical preventive activities.
4.	e-BI: In addition to receiving the same package as the control group, the e-BI group will be asked to refer identified at risk patients with an e-leaflet with unique log in codes to an approved e-BI specific package, which will be country specific, or, for Poland based on the WHO e-SBI program. The website should include the following: Log-in facility to allow monitoring of the patient (*i.e.*, patient actually log-in); suitable brief screening tool with ability to calculate score and give feedback (*i.e.*, brief intervention); appropriate information on sensible drinking guidelines; information on impact of alcohol on health and wellbeing; and a drink diary facility. Furthermore, the website could offer reminder facilities for follow-up activity.
5.	T&S and financial reimbursement: The T&S and financial reimbursement group will receive the package, T&S, and the financial reimbursement as described above.
6.	T&S and e-BI: The T&S and e-BI group will receive the package, T&S as above, and will be asked to refer identified at risk patients to e-BI as above.
7.	Financial reimbursement and e-BI: The financial reimbursement and e-BI group will receive the package and will be asked to refer identified at risk patients to e-BI as above. They will be paid for screening, referral performance to e-BI, and brief advice if actually delivered, with the system of pay as above.
8.	T&S, financial reimbursement and e-BI: The T&S, financial reimbursement and e-BI group will receive the package and T&S as above. They will be asked to refer identified at risk patients to e-BI as above. They will be paid for screening, brief advice activities, and referral performance to e-BI, with the system of pay as above.

A graphical depiction of the study is depicted in Additional file 1.

An introductory meeting (first briefing) will be held in all PHCUs that agree to participate in the study, describing the study’s purpose and the four-week baseline data collection, which will follow the introductory meeting. After the baseline data collection, all PHCUs will receive a second briefing within one month, either face to face or by telephone, tailor-made to the study group to which they are allocated.

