### Randomization and blinding

Randomization will take place after formal agreement of the PHCU to take part in the trial. The PHCU will be randomly allocated to one of eight groups by the European coordinating centre, using computerized randomization stratifying by country, ensuring 15 PHCUs per group (three per country). Although the PHCUs will be randomly allocated before the baseline measurement, the research team in each of the countries and the PHCU only are informed of the allocation after collection of the baseline measurement to avoid bias as a result of group allocation. For the remainder of the study period, the PHCU and investigators will not be blind to group allocation.

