### Statistical methods

Because of the hierarchical structure of the data (individual providers nested within PHCU nested within country), we will perform multilevel analyses of the screening and advice rates to examine the effect of the implementation strategies in comparison with the controls. The intention to treat analyses will include all participating providers (see above). Per protocol analyses will include only actively participating providers (see above). In all the analyses, we will use exposure to the implementation strategy as co-variate. Exposure is defined as positive if the providers meet the following criteria: financial—the PHCU received the financial reimbursement; e-BI—the provider handed out at least one referral card; and T&S—the provider attended the two face-to-face educational meetings. If these criteria will not be met, the exposure will be defined as negative.

Analyses will be performed in SAS V9.2 and based on mixed effects model (PROC GLIMMIX and PROC MIXED). We will use a random intercept model with fixed variables.

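### Training may be given to several PHCUs in one joint session, but the stated model has no session level, so the T&S standard error may be too small

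*Protocol article*

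**What the plan says.** Implementation strategies, Table 1 item 2, describes the training: "the T&S group will be offered two initial 1 to 2 hours face-to-face educational trainings". On location it says that arrangements differ by country and "include in-house meetings at the PHCU or within clusters of PHCUs". Trainers may be peers, members of the research team, accredited teachers or addiction consultants.

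Three further groups receive the same training under items 5, 6 and 8: "The T&S and financial reimbursement group will receive the package, T&S, and the financial reimbursement as described above"; "The T&S and e-BI group will receive the package, T&S as above"; "The T&S, financial reimbursement and e-BI group will receive the package and T&S as above". T&S therefore reaches four of the eight groups.

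The Statistical methods section describes the data as "individual providers nested within PHCU nested within country" and the model as follows: "We will use a random intercept model with fixed variables". It names no session or trainer level. The Sample size section uses one ICC, 0.029, and has no term for correlation between PHCUs.

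**The concern.** A session given jointly to several PHCUs creates a cluster above the PHCU. Those PHCUs hear the same trainer, do the same exercises and discuss the same barriers, so their later screening and advice rates may move together. This can happen only in groups 2, 5, 6 and 8.

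The stated model treats PHCUs as independent given country. The country intercept is common to trained and untrained PHCUs, so it largely cancels from the T&S contrast and cannot absorb a session effect confined to the T&S half. Where sessions are shared and outcomes correlate within them, the T&S effect would be tested against too small a standard error, and its confidence interval would be too narrow.

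**Working it through.** **Inputs from the article.** Randomization and blinding: "ensuring 15 PHCUs per group (three per country"). Four groups receive T&S, so 4 × 15 = 60 of the 120 PHCUs are trained, and 4 × 3 = 12 per country. Sample size: ICC 0.029, at least 1,000 eligible patients per PHCU per month, alpha 5% (taken as two-sided), 80% power.

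**The plan's own figures.** The design effect is 1 + 999 × 0.029 = 29.97. With a continuity-corrected comparison of two proportions:
- Screening, 8% v 12%: 932 patients per side; 932 × 29.97 / 1,000 = 27.9, so 28 PHCUs per side and 56 in total.
- Brief advice, 4% v 6%: 1,962 per side; 1,962 × 29.97 / 1,000 = 58.8, so 59 per side and 118 in total, or 120 when rounded up to a multiple of eight.

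The stated 56 and 120 are thus reproduced as comparisons of four groups with a strategy against four without it, with all PHCUs independent.

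**Allowing for shared sessions.** Let c be the number of PHCUs per session and r the correlation between the rates of two PHCUs in the same session. Both are assumptions. The T&S half then has its variance multiplied by 1 + (c − 1)r and the other half is unchanged. With equal halves and the same variance per PHCU in each:

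variance ratio V = [1 + 1 + (c − 1)r] / 2 = 1 + (c − 1)r / 2

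true type I error = 2 × [1 − Φ(1.96 / √V)]

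| c | r | V | true SE / model SE | type I error |
|---|---|---|---|---|
| any | 0 | 1.000 | 1.00 | 5.0% |
| 2 | 0.05 | 1.025 | 1.01 | 5.3% |
| 3 | 0.05 | 1.050 | 1.02 | 5.6% |
| 3 | 0.10 | 1.100 | 1.05 | 6.2% |
| 4 | 0.10 | 1.150 | 1.07 | 6.8% |
| 6 | 0.10 | 1.250 | 1.12 | 8.0% |

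In-house training has c = 1, so V = 1 and nothing changes.

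**Which outcome the table fits.** Suppose a share s of the between-PHCU variance belongs to the session. Then r = s × B, where B = m × 0.029 / [1 + (m − 1) × 0.029] is the between-PHCU share of the variance of a PHCU rate based on m patients.
- Screening, m = 1,000: B = 29 / 29.97 = 0.97, so r is close to s and the table applies.
- Brief advice: the Outcomes section divides by screen positives. If 8% to 12% of 1,000 are screened and 20% to 30% of those are positive (the positive share is an assumption), m runs from 80 × 0.20 = 16 to 120 × 0.30 = 36 per four-week block. B is then 0.464 / 1.435 = 0.32 to 1.044 / 2.015 = 0.52. With c = 3 and s = 0.10, V is 1.03 to 1.05 and the type I error about 5.4% to 5.6%.

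**The case against.** The strongest reply is that this is only a possibility. The article does not say how many PHCUs share a session, which countries train jointly, or how strongly outcomes correlate within a session. With two or three PHCUs per session and low correlation the distortion is slight. That stands, and it is why the point says that the standard error may be too small.

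A second reply is that an extra random term belongs in an analysis plan that is not shown. This stands in part. However, the article itself states both the delivery mode and the hierarchy, and the two do not match. The session identifier must also be captured during the trial, because an analysis plan cannot create it afterwards.

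Two stronger readings are tempting, and the article supports neither.
- A reader might infer a type I error above 10%. For example, c = 12 with r = 0.10 gives V = 1.55 and 11.5%. That needs all 12 T&S PHCUs of a country to act as one session, although Implementation strategies staggers the start date of each PHCU. An effect shared across a whole country is also better described as a country-by-T&S interaction. The Discussion accepts that strategy content differs by country, and fees and e-BI packages are country-specific too.
- A reader might infer that joint sessions mix allocation groups and contaminate the comparisons. The article does not say that groups are trained together, and three PHCUs of one group in one country could form a session. Everyone in a joint session is allocated to T&S, so the T&S contrast is untouched. Payment and log-in codes follow allocation, so attending a session transfers neither. Confining sessions to a single group would not help: it would confound session with group and move the variance inflation onto the reimbursement and e-BI contrasts.

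**Conclusion.** The point holds in conditional form. The article allows a mode of delivery that creates clusters of PHCUs in the T&S half only, and its stated model has no term for them. If sessions are shared and outcomes correlate within them, the T&S standard error is understated by a factor of about 1.01 to 1.12 for screening over the range c = 2, r = 0.05 to c = 6, r = 0.10. The nominal 5% error then becomes about 5.3% to 8.0%. For brief advice the inflation is smaller, to an extent that depends on the assumed number of screen positives. Where all training is in-house there is no inflation from shared sessions. Session size, correlation and the share of positives are all assumptions. The case for acting rests on the mismatch and the low cost of removing it, not on a demonstrated large bias.

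**What to change.** Record a session identifier and a trainer identifier for every T&S PHCU. T&S exposure is already defined by attendance at the two face-to-face meetings, so attendance has to be recorded anyway and this adds two fields to that record. In the analysis, add a random effect for session that applies to T&S PHCUs only (a partially nested model), with a PHCU trained alone counted as its own session. If the main model is to stay as stated, report this model as a sensitivity analysis.

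The cost is a slightly wider T&S interval and one more variance component. That component will be estimated from few sessions and so will be imprecise.
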